# A multi-centre, pragmatic, three-arm, individually randomised, non-inferiority, open trial to compare immediate orally administered, immediate topically administered or delayed orally administered antibiotics for acute otitis media with discharge in children: The Runny Ear Study (REST): study protocol

**DOI:** 10.1186/s13063-020-04419-7

**Published:** 2020-06-03

**Keywords:** Acute otitis media, Primary care, Antibiotics, Paediatrics, Randomised controlled trial

## Abstract

**Background:**

Acute otitis media (AOM) is a common painful infection in children, with around 2.8 million cases presenting to primary care in England and Wales annually. Nearly all children who present to their general practitioner (GP) with AOM or AOM with discharge (AOMd) are treated with orally administered antibiotics. These can cause side effects; contribute to the growing problem of antimicrobial resistance, and more rarely, allergic reactions. Alternative treatments, such as an antibiotic eardrops, or ‘delayed’ orally administered antibiotics, could be at least as effective and safe as immediate orally administered antibiotics for children with AOMd.

**Methods/design:**

REST is a pragmatic, three-arm, individually randomised, non-inferiority trial being conducted in 175 GP practices across the United Kingdom (UK). The study aims to recruit 399 children aged (≥ 12 months and < 16 years) presenting to their GP with AOMd. Children will be randomised to one of three arms: immediate ciprofloxacin 0.3% eardrops; delayed orally administered amoxicillin (clarithromycin if penicillin allergic) or immediate orally administered amoxicillin (clarithromycin).

Recruitment, including eligibility screening, randomisation and data collection, are conducted using the innovative, TRANSFoRm electronic trial management platform. Integrated within the primary care electronic medical records it provides automatic eligibility checking, part-filling of e-CRFs, study workflow management and routine NHS follow-up data collection. The primary outcome is time to resolution of all significant symptoms and will be collected by the parent using a Symptom Recovery Questionnaire (SRQ). Secondary outcomes, including cost-effectiveness, duration of moderately bad or worse symptoms and repeat AOMd episodes, will be collected at day-14 and at 3 months.

**Discussion:**

It is unclear whether prescribing orally administered antibiotics to children with AOMd results in a reduction in symptoms or a shorter duration of illness. The REST trial should allow us to compare the non-inferiority of: immediate topically administered ciprofloxacin ear drops, or delayed orally administered amoxicillin (clarithromycin) against immediate orally administered amoxicillin (clarithromycin). We aim to recruit 399 patients from 175 practices in the UK. Using the TRANSFoRm software to randomise participants to the trial will enable recruitment for a relatively uncommon condition.

**Trial registration:**

Name of Registry: ISCRTN

Registration Number: ISRCTN12873692. This contains all items required to comply with the World Health Organization Trial Registration Data Set

Date of Registration: 24 April 2018

Name of Registry: EudraCT

Registration Number: 2017-003635-10

Date of Registration: 6 September 2017

## Background and rationale

Acute otitis media (AOM) is important to children, parents and the National Health Service (NHS). Firstly, the infection causes pain and distress to the child, disrupting sleep and family routines. In around 15% of cases, a rise in middle-ear pressure and/or inflammation weakening the tympanic membrane results in it bursting, discharging pus from the middle ear as a discharge (otorrhoea) [1]. Children with AOM and discharge (AOMd) have similar levels of pain and are more unwell at presentation than children with AOM [2, 3]. Moreover, children with AOMd have a worse prognosis, and higher rates of pain at 1 week, as reported by parents (carers), repeat AOM episodes and hearing problems at 3 months [2]. Estimates of parental costs (travel, over the counter (OTC) medicines and lost earnings) vary [4–6], with even the lowest suggesting £4 million in England and Wales per annum.

Over 90% of UK parents attend primary care health services for each episode of AOMd [7], with over 150,000 general practitioner (GP) consultations for AOMd in England and Wales per annum at a cost to the NHS of over £3 million [4, 5], which is more than for any other common symptom of acute infection.

More children with AOM and AOMd receive an orally administered antibiotic in the UK [8] and the United States [9] than for any other respiratory infection, with three quarters of GPs prescribing orally administered antibiotics to at least 80% of children diagnosed as such [10, 11]. Our 2015 audit, including 33 GP practices and 56,251 children, confirmed that immediate orally administered antibiotics is usual care for AOMd: 88% were given orally administered antibiotics of which 97% were given immediately.

There is strong evidence that children with AOMd benefit from immediate orally administered antibiotics. The number needed to treat with antibiotics is three to reduce the proportion of children with pain and/or fever at 3–7 days compared with placebo/no treatment [3]. The National Institute for Health and Care Excellence (NICE), therefore, recommends that immediate antibiotics should be considered [12]. Orally administered antibiotics do, however, also cause side effects, are associated with subsequent eczema and hay fever [13] and with population [14] and patient-level [15] antimicrobial resistance.

In response to the UK’s Antimicrobial Resistance Action Plan calls for research to preserve antibiotic effects [16] we have designed a trial of topically administered antibiotics in children with AOMd, aiming to reduce the use of systemic antibiotics. Perforation of the tympanic membrane provides a portal of entry into the middle ear for antibiotic drops instilled in the ear canal. In children with ventilation tubes (‘grommets’), it has been shown that topically administered antibiotics can reach the infected middle ear despite purulent discharge [17], and that compared with orally administered antibiotics, they are more effective in reducing the duration of otorrhoea, recurrence of AOM and have fewer side effects [17]. This study also showed that topically administered antibiotics are cost-effective [18]. However, further research is needed in children with AOMd without grommets, since the opening to the middle ear may be smaller and the tympanic membrane heals quickly, which could prevent the drops from reaching the middle ear. If topically administered and delayed antibiotics are shown to be non-inferior, we also need to understand the acceptability of such treatment to clinicians and parents and how to address any barriers to implementation.

We will address this evidence gap by assessing the clinical effectiveness and economic implications of immediate topically vs. delayed orally administered antibiotics and testing the hypotheses: (1) immediate antibiotics are better than placebo/no treatment for AOMd symptoms [3] and (2) delayed orally administered antibiotics are similar to immediate orally administered antibiotics in children with AOM (though with reduced antibiotic consumption) [1].

The REST study is a three-arm, randomised controlled trial (RCT) investigating the clinical effectiveness and economic implications of topically administered or delayed antibiotics compared with immediate orally administered antibiotics, powered for the duration and severity of the symptoms most important to parents, while also investigating adverse events, complications and AOM/AOMd recurrence. By testing two interventions that could reduce systemic antibiotic exposure (immediate topically administered and delayed orally administered antibiotics), this study is at the forefront of research to improve antimicrobial stewardship in AOMd.

## Methods/design

### Aims and objectives

The key aim of this research is to investigate the clinical effectiveness and economic impact of immediate topically or delayed orally administered antibiotics compared with immediate orally administered antibiotics for symptom duration in children presenting to primary care with AOM with discharge (AOMd).

Secondary objectives are to:
Estimate the short-term cost-implications of immediate topically or delayed orally administered antibiotics compared with immediate orally administered antibiotics from the perspective of the NHSCompare the effects on duration of ‘moderately bad or worse’ symptoms; parent/legal guardian satisfaction with treatment; and adverse eventsCompare hearing loss and rate of recurrence of AOM/AOMd at 3 monthsUnderstand parent/legal guardian and clinician views of participating in a trial about AOMd, adherence and satisfaction with allocated treatment.Evaluate the impact of treatment on carriage of antibiotic resistance in the gut

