### Interventions

#### Choice of comparator

We selected ciprofloxacin 0.3% drops as our topically administered antibiotic because it:
Is active against all common otopathogens [2]Is non-ototoxicIs widely and routinely available in the UKIs colourless so will not interfere with assessing otorrhoeaWill provide complementary evidence to the ZonMw-funded trial, which is using an antibiotic-steroid combination

We decided to avoid aminoglycoside drops because of concerns about potential ototoxicity. We have proposed delayed orally administered antibiotics as the second intervention since our previous trials [1, 20, 21] have achieved significant reductions in orally administered antibiotic consumption compared with immediate antibiotic prescribing (and similar symptom relief). Immediate orally administered amoxicillin (clarithromycin if allergic to penicillin) is the comparator as it reflects usual care and is well-tolerated.

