#### Intervention description

Arm 1: (control) current usual care – orally administered amoxicillin suspension three times daily for 7 days (or orally administered clarithromycin twice daily for 7 days if allergic to penicillin).

Arm 2: (intervention) antibiotic drops, to be instilled three times daily into the discharging ear. Parents will be given written advice regarding how to administer the drops. This will include: (1) cleaning the outer ear of discharge that can be easily removed with a tissue; (2) tilting the child’s head to one side (to approximately 90°) when applying the eardrops; and (3) maintaining the tilt for a few minutes to improve penetration of the drops.

Arm 3:(intervention) a ‘delayed’ prescription for orally administered amoxicillin suspension antibiotics three times daily for 7 days (or orally administered clarithromycin twice daily for 7 days if allergic to penicillin). Parents will be given written advice to delay the prescription will consist of: (1) advising that the prescription is only ‘dispensed’ at a pharmacy if symptoms worsen or are not starting to improve by 4 days; and (2) safety-netting advice regarding the symptoms that should prompt review consultation (increasing pain, high temperatures, headaches, irritability or reduced feeding).

All groups will also receive standard advice to complete the antibiotic course and how to manage pain, fever and other symptoms (e.g. use of paracetamol/ibuprofen).

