### Outcome measures

The primary outcome measure is time to resolution of the following symptoms: pain, fever, being unwell, sleep disturbance, otorrhoea and episodes of distress. The primary outcome is the time until all symptoms are rated by parents as ‘no’ or ‘very slight’ problem. This will be recorded by parents in the Symptom Recovery Questionnaire (SRQ).

Secondary outcome measures:
Duration of ‘moderately bad or worse’ symptoms (pain, fever, being unwell, sleep disturbance, otorrhoea; episodes of distress/cryingAppetite and interference with normal activities up to 14 daysAntibiotic and analgesic useAdverse events – diarrhoea, rash, vomiting, serious complicationsTreatment adherenceParent/legal guardian satisfaction with treatmentNHS resource use at 14 daysRepeat AOM and AOMd episodes, serious complications and the OM6 hearing questionnaire at 3 months;Qualitative evaluation of recruitment, medication satisfaction, adherence and follow-upAnalysis of stool sample to assess burden of resistance

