### Trial oversight

The study is overseen by a Trial Management Group that meet on a monthly basis and consist of the chief investigator (CI), grant holders, study sponsor and any other staff responsible for the delivery of the trial. The Trial Steering Committee (TSC) provides independent supervision of the trial and oversees trial progress. The TSC consists of an independent chair and three other independent members including a clinical trialist a statistician, a Patient and Public Involvement (PPI) representative and the CI. The Data Monitoring Committee (DMC) monitors patient safety and trial data efficacy and consists of an independent chair, three other independent members and the CI.

All serious adverse events (SAE’S) are recorded and notified as appropriate to the relevant authorities.

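### The adverse-event outcome names no local ear reaction, which tilts the planned safety comparison of eardrops with immediate oral antibiotics towards drops by an unknown amount

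*Protocol article*

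**What the plan says.** Aims and objectives (protocol article) sets a secondary objective whose items include "parent/legal guardian satisfaction with treatment" and, next to it, adverse events. No event is named there. The naming is done under Outcome measures, where the adverse-event line consists of diarrhoea, rash and vomiting as non-serious events, together with serious complications. The line has no wording such as 'for example' or 'other'.

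Under Intervention description, the control arm takes "orally administered amoxicillin suspension three times daily for 7 days" (clarithromycin if allergic to penicillin), and the drops arm receives "antibiotic drops, to be instilled three times daily into the discharging ear". The delayed arm uses the same oral drugs as control.

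Ear-related safety was considered when the drug was chosen. Choice of comparator states: "We decided to avoid aminoglycoside drops because of concerns about potential ototoxicity".

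Side effects are also part of the rationale. The Background says: "Orally administered antibiotics do, however, also cause side effects". For topical against oral treatment in children with grommets, it reports advantages that include "recurrence of AOM and have fewer side effects".

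**The concern.** The three named non-serious events are general effects of the kind expected from a swallowed antibiotic, although rash is not specific to that route. The list has no counterpart for a treatment put into the ear canal. A child whose ear itches or is irritated after drops contributes nothing to the adverse-event outcome, while a child with loose stools after amoxicillin does.

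The safety result is a secondary outcome, but it bears on how the trial is read. In a non-inferiority trial, the reason to prefer a new treatment that is not worse on symptoms lies elsewhere: here in less systemic antibiotic exposure and, by the Background's own account, fewer side effects. The earlier evidence on side effects comes from children with grommets, and the article says that children without grommets need further research. A lower count of listed events under drops could easily be reported as better tolerability overall, which this list cannot show.

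**Working it through.** No adverse-event rate is stated, so there is no plan figure to reproduce. The check is to follow a mild, non-serious local reaction to drops through everything the article says is measured.

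| Measurement (section) | What it captures | Counted as an adverse event? |
|---|---|---|
| Adverse-event outcome (Outcome measures) | Three general non-serious events, and serious complications | A local reaction is not on the list |
| Daily SRQ, primary outcome (Outcome measures) | "pain, fever, being unwell, sleep disturbance, otorrhoea and episodes of distress" | No. Stinging rated as pain or distress counts as unresolved illness. Itching is not among these symptoms |
| OM6 at 3 months (Outcome measures; Patient-reported outcomes) | Parent-reported hearing loss | No. It does not measure short-term local tolerability |
| Serious events (Trial oversight) | "All serious adverse events (SAE’S) are recorded and notified as appropriate to the relevant authorities" | Serious local events are recorded, mild ones are not |
| Adherence, satisfaction, analgesic use (Outcome measures); interviews (Qualitative data collection) | Indirect signs of poor tolerability | No |

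So pain, discharge, distress, hearing and serious harm are seen in all arms. What goes uncounted is mainly mild irritation, itching or discomfort.

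**Which comparison is affected.** Drops against immediate oral differ in route, so the omission is one-sided. Delayed against immediate oral share the route, so it is not.

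**Illustration with assumed rates.** Let *s* be the risk of a listed event and *l* the risk of a local reaction, taken as independent. Then

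any-event risk = 1 − (1 − *s*)(1 − *l*).

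Assume *s* = 20% for oral and 10% for drops. On listed events alone, drops are better by 20 − 10 = 10 points.

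- Drops with *l* = 5%, 10%, 15%, 20%: 1 − 0.90 × 0.95 = 14.5%; 1 − 0.90 × 0.90 = 19.0%; 1 − 0.90 × 0.85 = 23.5%; 1 − 0.90 × 0.80 = 28.0%.
- Oral with background *l* = 0%, 5%, 10%: 20.0%; 1 − 0.80 × 0.95 = 24.0%; 1 − 0.80 × 0.90 = 28.0%.

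Difference, oral minus drops, in points (positive favours drops):

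| Local rate, drops | Oral background 0% | 5% | 10% |
|---|---|---|---|
| 5% | 5.5 | 9.5 | – |
| 10% | 1.0 | 5.0 | 9.0 |
| 15% | −3.5 | 0.5 | 4.5 |
| 20% | −8.0 | −4.0 | 0.0 |

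Where the local rate is the same in both arms, the 10-point gap hardly moves (9.5 or 9.0). What matters is the excess of local reactions under drops, about which the article gives no information.

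**The case against.** The strongest reply is that this is a journal article. The full protocol (Version 7.0 according to Trial status), the adverse-event form and the SRQ are not shown, and a one-line outcome may condense a longer list. That stands as a caution: if the full form already records local reactions, only the published list needs to be brought into line. It does not remove the point, because the article names specific events, and the set it names is uneven between routes. That differs from leaving the detail to another document.

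Second, local harm is far from invisible. Comparing hearing loss at 3 months is a stated objective, which answers much of the ototoxicity concern. Stinging scored as pain or distress would delay resolution and so count against drops in the primary outcome. This stands, and it narrows the point to mild reactions. It does not repair the safety comparison, because a treatment effect recorded as slow recovery is still not recorded as a harm.

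Third, a reader might infer from the first column of the table that the true safety ranking is reversed. The documents do not support that. All the rates are assumed, an any-event composite is defined nowhere in the article, and zero background in the oral arm is implausible when every child has a discharging ear.

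Fourth, asking unblinded parents about reactions linked to treatment would invite them to blame the drops and create the opposite bias. This is right, and it determines how the item should be worded.

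**Conclusion.** The point holds in a limited form. As the outcome is written, the comparison of adverse events between drops and immediate oral antibiotics is tilted towards drops, because non-serious local reactions are not on the list. The direction follows if drops cause any excess of such reactions. The size is unknown, and the illustration shows only that it could range from negligible to material.

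A reader might go further and say that drops must look safer by construction. The text does not support that: serious complications are on the list and can count against any arm, rash is not exclusive to oral treatment, and the list leans the comparison without fixing its result. Nor does the article announce a planned claim of fewer adverse events; the risk lies in how the result is later read.

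The conclusion assumes that the listed events are the ones compared, as the Outcome measures section reads. It affects a secondary safety conclusion, not the primary analysis.

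**What to change.** Add a local ear reaction item to the adverse-event line under Outcome measures: new or worse irritation, itching or discomfort of the ear or ear canal. Ask it in identical words in all three arms at the day-7 and day-14 calls already scheduled, without asking parents whether the treatment caused it. The oral arms then supply the background rate. Report it by type, beside the events already listed.

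If the item cannot be added (Trial status reports recruitment closed with 22 children), describe the comparison as covering the listed events only, and do not conclude from it that drops cause fewer adverse events overall.

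The cost is one question at two existing calls and one eCRF field. Parent reports remain unblinded, so some reporting bias is unavoidable even with neutral wording, and the safety result for drops may look slightly less favourable. The fallback costs one sentence in the report.

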### Trial design

This is a multi-site, pragmatic, three-arm, individually randomised (stratified by age < 2 vs. ≥ 2 years), non-inferiority, open trial. We compare (1) immediate topically administered ciprofloxacin 0.3% drops with (2) delayed orally administered antibiotics or (3) immediate orally administered antibiotic in children aged 12 months to 16 years with unilateral AOMd as the presenting symptom of recent-onset (≤ 7 days) AOM. The primary endpoint is collected by questionnaire at day 14 post recruitment. Secondary outcomes are collected both at 14 days and at 3 months by questionnaire.

This study is classified as a Type A study (low risk) by the Medicines and Healthcare Regulatory Agency (MHRA), with regulatory approval obtained on 4 May 2018.

The trial design includes an internal pilot recruitment phase of 6 months’ duration, primarily to verify that recruitment was possible before progression to the main phase of the trial.

The REST study utilises an integrated electronic trial management platform, TRANSFoRm, that was initially developed as part of the EU FP7 TRANSFoRm project (2009–2015) and evaluated in a 60-site clinical trial in Poland [19]. The system integrates as a plug-in within the host Electronic Health Record (EHR) system through the provider’s Application Programmer’s Interface (API). The key features of the system include:
Automated eligibility checking; the TRANSFoRm plug-in allows the EHR opened during a consultation to be automatically checked against the REST eligibility criteriaConsent – the TRANSFoRm platform allows the clinician to print the study consent form for the participant to sign a record of consent that can then be entered onto the platform initiating the trial’s workflowAn integrated randomisation system for immediate randomisation of participants during consultationTrial-specific Electronic Case Report Forms (eCRFs) that are presented to clinicians at the appropriate appointments to complete. Some trial data is automatically retrieved from the SystmOne health record and used to part-fill the trial eCRF, which can be amended by the user

Upon submission of the eCRF the TRANSFoRm platform automatically records a record of trial activity in the participant’s health record. The study flow diagram is provided in Fig. 1 and the Standard Protocol Items: Recommendations for Interventional Trials (SPIRIT) Checklist in Additional file 1.

